### Recruitment and screening

Chart review and team meetings will be used to identify outpatients at the academic medical institution and at the private clinic who meet criteria for the proposed study diagnoses. The research team will speak with the patient’s psychiatrist and that individual will inform the research team whether they believe the patient can comprehend the study and procedures. If they deem the patient can provide informed consent and understand the study, the patient will be approached by someone familiar to them (e.g., a member of their care team) to see if they are willing to discuss participation in this study. If the patient assents, their name will be given to a research staff member who will contact them to schedule a study session. Patients may be pre-screened by phone. Research personnel involved with recruitment will discuss the study with the patient. If the participant meets criteria for the study, they may be scheduled for participation in the study. Research participants may be recruited through inpatient, partial hospital, intensive outpatient, or other clinics.

### Randomization and blinding procedures

Randomization will be stratified by site, with independent allocation sequences generated within each site. Within each stratum, treatment assignments will be generated using a permuted block design to maintain balance between groups throughout enrollment. The study biostatistician (SV) will generate the randomization sequence. As this is a single-blind study, study personnel responsible for administering TMS will have access to the allocation sequence, maintained on a central electronic document, and will not be blinded to treatment assignment. Participants will remain blinded to the intervention they receive throughout the duration of the study. Sham (placebo) stimulation will be delivered by flipping the coil 180 degrees so that the procedure mimics the look and sound of active stimulation but deliver no stimulation to the participant. Participants will only be un-blinded if an adverse reaction to active TMS occurs and the participant can no longer remain enrolled in the study. We will make numerous attempts to retain participants in the study with phone calls, emails, and text messages.

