## Methods

### Study design

The study is a randomized, single-blind, sham controlled clinical trial of iTBS to reduce opioid craving in people diagnosed with OUD who are currently receiving treatment with buprenorphine. The study consists of 12 study visits. Participants will also have the option to elect to participate in optional MRI scans before and after the intervention. At the first visit (Consent), participants will complete informed consent, which will be obtained by the researcher conducting the study. After completing consent, participants will undergo additional screening procedures to ensure safety to receive TMS (and safety to receive MRI if the participant elects to complete these scans) and will complete questionnaires (listed in Fig 1) about substance use and psychiatric symptoms. Enrolled participants will then undergo 8 weekly sessions of left DLPFC-targeted iTBS. Prior to the first TMS visit, individuals will be randomized to receive active or sham iTBS. At each TMS visit, participants will complete questionnaires about their substance use and psychiatric symptoms and provide a sample for urine toxicology. After the 8-week TMS intervention, participants will return for follow-up visits at weeks 10, 12, and 20. At each follow-up visit, participants will complete questionnaires about their substance use and psychiatric symptoms and provide a sample for urine toxicology. If a participant elects to undergo the optional MRI visits, they will undergo 2 MRI scans 1) before the first TMS visit; and 2) after the week 8 TMS visit. During both MRI scans, participants will complete a resting state fMRI and perform a task assessing cue reactivity in the scanner. At these sessions, participants will also complete tasks outside the scanner assessing inhibitory control and reward processing. See Figs 2 and 3 for a visualization of the study design and Fig 1 for a list of assessments conducted on each study visit. This protocol was developed with input from multiple certified peer recovery specialists ([name], [name], [name]), who are coauthors on this manuscript and have lived experience with substance use.

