### Inclusion and exclusion criteria

*Inclusion*
*criteria*

Age between 18–65 yearsDiagnosis of OUD according to DSM-5 criteria and confirmed by SCID [27]Currently prescribed buprenorphine for opioid use disorderMeets either of the following criteria: (1) reports opioid craving of 2 or greater on a 0–10 scale, or (2) has returned to opioid use at least once within the past 12 monthsMust be able to read, speak and understand EnglishMust be judged by study staff to be capable of completing the study proceduresParticipants will be in stable outpatient psychiatric treatment and psychiatrically stable.

*Exclusion*
*criteria*

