### Statistical analysis plan

#### Primary outcome analysis.

A change in craving score (Δcraving) on the OCS will be calculated between pre-TMS (week 1 timepoint) and post-TMS (week 10 timepoint) and a linear model will determine whether Δcraving significantly differs between active and sham conditions (controlling for age, sex, and pre-TMS craving). Change in number of days of use on the TLFB (Δuse) will be calculated between pre-TMS (week 1 timepoint) and post-TMS (week 10 timepoint) and a model will determine whether Δuse significantly differs between active and sham conditions (controlling for age, sex, and pre-TMS days of use). In post hoc analyses, we will investigate the effects of buprenorphine dose in response to TMS.

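### TMS operators are given the allocation sequence itself, and assignment precedes the week-1 baseline, so allocation is not concealed from them and bias could enter before treatment starts

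*Protocol article*

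**What the plan says.** Randomization and blinding procedures (protocol article) stratifies by site, uses permuted blocks within site, and has the study biostatistician generate the list. It then says, as a consequence of the single-blind design, that "study personnel responsible for administering TMS will have access to the allocation sequence, maintained on a central electronic document", and that these staff are not blinded.

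On timing, Study design states: "Prior to the first TMS visit, individuals will be randomized to receive active or sham iTBS". The same section says: "At each TMS visit, participants will complete questionnaires about their substance use and psychiatric symptoms and provide a sample for urine toxicology".

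On the baseline, Primary outcome analysis says that the craving change score "will be calculated between pre-TMS (week 1 timepoint) and post-TMS (week 10 timepoint) and a linear model will determine whether" the arms differ. The change in TLFB days of use has the same two timepoints. Each model adjusts for age, sex and its own pre-TMS value.

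On discretion at entry, one inclusion criterion is that the participant be "judged by study staff to be capable of completing the study" procedures. The exclusion criteria add an investigator's opinion on suitability and a case-by-case physician decision on medications.

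**The concern.** Blinding and allocation concealment are separate protections. Blinding concerns who knows the arm once a participant is assigned. Concealment concerns whether anyone can know the next assignment before the next participant is irrevocably entered. The article cites the single-blind design as the reason for giving operators the sequence, but that design justifies only knowledge of the current participant's arm.

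If a person who can see the next assignment also influences who is approached, judged suitable or booked next, the arms can come to differ in prognosis. Adjustment for age, sex and one baseline measure does not remove differences in unmeasured prognosis, and no later analysis restores concealment.

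The timing adds a second, smaller exposure. The reference value for both primary outcomes is collected after assignment, at a visit attended by staff who may know the arm.

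**Working it through.** The article states no figure on this point, so the check is mainly a reading of sections against each other, followed by one illustration of scale.

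**1. What the operators can see.** The object of access in Randomization and blinding procedures is the sequence, kept in a central electronic document. Nothing in that sentence limits access to participants already enrolled. Read as written, future assignments are visible.

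**2. When the baseline is taken.** Study design gives 12 visits: 1 consent + 8 TMS + 3 follow-up (weeks 10, 12 and 20) = 12. It also refers to a week 8 TMS visit, so the TMS visits are weeks 1 to 8 and week 1 is the first of them. Randomisation comes before that visit, and the primary analysis takes its pre-TMS value from week 1. The order is therefore consent and screening, then randomisation, then the week-1 baseline, then stimulation. Questionnaires are also completed around the consent visit, before randomisation, but the primary analysis does not take its baseline from there.

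**3. Where foreknowledge could act.** Eligibility includes judgements by study staff, the investigator and the covering physician (Inclusion and exclusion criteria). Candidates are found through chart review and team meetings, and a research staff member schedules them (Recruitment and screening). The article does not say whether TMS operators take part in any of these steps.

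**4. How a baseline distortion would carry through.** Let Y1 and Y10 be the week-1 and week-10 values. With Y1 as a covariate, the arm coefficient for Y10 − Y1 equals the arm coefficient for Y10:

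effect = (mean Y10 active − mean Y10 sham) − β × (mean Y1 active − mean Y1 sham),

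where β is the within-arm slope of Y10 on Y1. An artificial arm difference δ in the recorded baseline shifts the estimate by −βδ. It enters once, through the slope, although the baseline appears both in the change score and as a covariate.

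**5. Illustration of scale.** Inputs: 100 completers (Sample size), taken as 50 per arm (equal allocation is assumed), and a 5% type 1 error, taken as two-sided (assumed). The bias b, in SD units, is an assumption.

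- Standard error of the contrast: √(2/50) = 0.20 SD.
- False-positive rate: 1 − Φ(1.96 − b/0.20) + Φ(−1.96 − b/0.20).

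| Assumed bias b (SD) | b/0.20 | False-positive rate |
|---|---|---|
| 0 | 0 | 5.0% |
| 0.05 | 0.25 | 5.7% |
| 0.10 | 0.50 | 7.9% |
| 0.20 | 1.00 | 17.0% |
| 0.30 | 1.50 | 32.3% |

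For comparison, Sample size states a detectable effect of 0.40. If that figure is in SD units, which the article does not say, biases of 0.10 and 0.20 would be a quarter and a half of it.

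**The case against.** The strongest reply is that no route to selection bias is shown. The article describes the operators as trained technicians. It assigns the comprehension judgement to the patient's psychiatrist, the first approach to someone familiar to the patient, scheduling to a research staff member, consent to the researcher conducting the study, and suitability to the investigator. Delegation of duties is commonly left to the full protocol. This stands. A reader might infer that operators recruit or screen, or that allocation is open to everyone at the sites, but the article says neither. Loss of concealment is shown for the operators only.

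A reader might also infer that unblinded staff collect the TLFB by interview and can steer it. The article states neither its mode nor its administrator. Craving is a visual analogue rating, and participants remain blinded. The week-1 value is also labelled pre-TMS. The measurement risk at baseline is therefore modest.

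A third tempting inference is that a distorted baseline does double damage because it is used twice. Step 4 of the working shows that it does not.

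Finally, operator unblinding is a declared feature of the design and is not the fault. What the reply leaves untouched is the sentence on access. It is a stated rule rather than an omitted detail, and single-blinding does not require it.

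**Conclusion.** The point holds as a risk created by the stated procedure, not as a demonstrated bias. Two facts rest on the text: operators have access to the sequence, and assignment precedes the week-1 baseline of both primary outcomes. Whether bias follows depends on something the article does not state, namely whether operators, or others who can open the document, have any part in eligibility, scheduling or baseline collection.

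The size cannot be derived from the article. The figures of about 8% and 17% for biases of 0.10 and 0.20 SD show only how sensitive a trial of 50 per arm would be. They rest on an assumed bias, equal allocation and a two-sided test.

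This should be fixed: it is inexpensive to change now, and lost concealment cannot be repaired in the analysis.

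**What to change.** Amend Randomization and blinding procedures so that the sequence is held by the biostatistician, or in a randomisation module closed to site staff. One participant's assignment is released to the operator only after three things are recorded: consent, confirmed eligibility, and the week-1 OCS and TLFB completed before stimulation. Align the timing sentence in Study design with this, since assignment would then fall at the first TMS visit rather than before it.

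No change to block sizes or to the mode of questionnaire completion is asked for, because the article does not state either.

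The cost is a small procedural amendment at two sites under two ethics boards, and assignment released on the day of the first TMS visit. Sample size and number of visits are unaffected. Participants already randomised cannot be corrected. Recruitment opened in June 2026 and is projected to run to June 2028, so a prompt change would cover most of the enrolment period.

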### Intervention

#### iTBS equipment.

The study will use the MagVenture MagPro X100 with MagOption (VUMC) or MagPro R30 (SynapticPSYCH) system equipped with a Cool-B70 butterfly coil to determine motor threshold and to administer the iTBS intervention. Active stimulation will be delivered with the coil in the active orientation. Sham stimulation will be delivered by flipping the coil 180 degrees so that this condition will look and sound like active stimulation but deliver no stimulation to the participant. TMS will be administered by Bachelors-level trained technicians under the supervision of a board-certified psychiatrist at both sites.

#### iTBS treatment dose and frequency.

Participants will receive 2 sessions of iTBS per study visit. iTBS will be delivered at 100% of resting motor threshold, which will be determined before the first iTBS of each study visit. Resting motor threshold (RMT) will be obtained by following recommendations from the International Federation of Clinical Neurophysiology [28], which is defined as the lowest stimulus intensity required to elicit a visible motor twitch of the abductor pollicis brevis in 5 out of 10 consecutive trials. The iTBS intervention will use FDA-cleared parameters for depression [29,30]. On each study day, iTBS will be applied over the left DLPFC twice, with each application consisting of 1800 pulses (60 cycles of ten 50-Hz triplets delivered in 2-second trains (5 Hz) with an 8-second intertrain interval). This protocol will occur twice per day (3600 pulses per day), separated by a 50-minute interval, which has been shown to be a safe and effective spacing interval for iTBS [29,30]. This schedule will thus deliver a total of 28,800 pulses over 8 weeks (16 sessions).

### Monitoring

An independent safety monitor (ISM) will review this study for safety and adherence to the study protocol. The ISM will meet with the study PI every 6 months to assure safety of research participants, regulatory compliance, and data integrity. The ISM is distinctly separate from the role of the PI. A report will be generated after every ISM meeting and communicated with the IRB if needed. The ISM will review any seizure in order to assess what new precautions may be needed for subsequent subjects. A single occurrence of one of the following will trigger stopping the study, immediate ISM assessment, and FDA notification: seizure, status epilepticus, attempted or completed suicide. All participants will also be monitored throughout the study for any adverse reactions in relation to the TMS using the Adverse Reaction Form for TMS. Adverse reactions will be reviewed by a physician daily prior to TMS and then following TMS. The TMS sessions will be discontinued if the psychiatrist evaluates this side effect to be a worsening related to TMS application and the patient’s treating psychiatrist will be contacted if clinically indicated.

### Study status and timeline

Participant recruitment commenced on June 1^st^ 2026 at both study sites and remains ongoing as of August 2026. Recruitment is projected to be completed in June 2028. Final data collection is expected to conclude in November 2028, and study findings are anticipated to be available in December 2028.

### Outcomes and assessments

#### Primary outcome.

The primary outcome is to determine the effects of active left DLPFC targeted iTBS compared to sham on craving and opioid use in 100 people with OUD. Specifically, this study seeks to provide evidence that L DLPFC-targeted iTBS leads to reduced craving and opioid use in individuals with OUD.

Participants’ craving and drug use will be assessed prior to receiving iTBS, during iTBS intervention and following the end of iTBS (10, 12 and 20 weeks). Craving will be measured using the Visual Analogue Scale (VAS) on the Opioid Craving Scale (OCS). Opioid use will be measured as the number of days of use in the preceding week using the Timeline Follow Back (TLFB).

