**Aims:**

Our primary aim is to determine whether 16 sessions of active iTBS applied to the left DLPFC results in reduced craving and opioid use, and higher treatment retention, relative to sham. In a secondary aim, we will also examine whether iTBS-related changes in craving are associated with changes in functional connectivity between the left DLPFC and both the dorsal striatum and anterior cingulate cortex.

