Is TMS for OUD effective, and if so, how does it exert its effects? Only one study of TMS for OUD has included neuroimaging [24], despite neuroimaging being critical for helping to characterize the neural circuit changes that occur with TMS treatment.Is a weekly dosing schedule of TMS for OUD a feasible and acceptable adjunctive treatment? A previous study [26] testing therapeutic TMS protocols (i.e., daily sessions of treatment over multiple weeks) struggled with recruitment and retention, questioning the feasibility and acceptability of this intervention for this population.Can we provide TMS for populations with OUD beyond urban academic medical centers? Expanding access to TMS has been a challenge for the field more broadly, besides the treatment of SUDs. While clinical trials for TMS are typically conducted in academic medical centers, more widespread clinical application would ultimately require delivery of TMS for SUDs in private outpatient clinics nationwide.

To address these questions, we designed a multi-site randomized controlled trial of TMS for OUD among individuals receiving buprenorphine treatment. We will implement a novel weekly stimulation protocol designed to improve treatment efficiency and better align TMS delivery with routine weekly clinic visits. The trial will be conducted across both an academic medical center and private practice clinics throughout Tennessee to help address the question of clinical applicability beyond academic medical settings. Our central hypothesis is that DLPFC-targeted iTBS will significantly reduce both opioid craving and opioid use. In secondary analyses, we will use neuroimaging (MRI) to assess whether a change in functional connectivity between the DLPFC and both the dorsal striatum and anterior cingulate cortex (ACC) is associated with reductions in craving. Ultimately, this work aims to establish a safe and effective adjunctive therapy to directly mitigate the severe craving and high relapse rates that limit current OUD treatments.

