### Sample size

We plan to recruit up to 60 participants at each site (VUMC and SynpaticPSYCH) to obtain a completion sample of n = 50 at each site for a total of n = 100. With 80% power, a type 1 error rate of 5%, and 100 subjects across all sites, we can detect effect sizes larger than 0.40. Based on these calculations, our proposed total sample of n = 100 will provide adequate power to detect changes in craving and opioid use.

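### Craving and opioid use are joint primary outcomes tested separately with no decision rule, so the single 5% error and 80% power are not tied to a primary conclusion; retention is in the primary aim without an outcome or test

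*Protocol article*

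**What the plan says.** - **Primary outcome** (Outcomes and assessments): the effect of active iTBS "compared to sham on craving and opioid use in 100 people with OUD". Craving is scored on the Opioid Craving Scale. Opioid use is days of use in the preceding week on the Timeline Follow Back.
- **Primary outcome analysis** (Statistical analysis plan): two models, one for change in craving and one for change in days of use, both from week 1 to week 10 and adjusted for age, sex and the baseline value. Each is to decide whether the arms differ significantly. No significance level, order or link between the two tests is given.
- **Sample size**: "With 80% power, a type 1 error rate of 5%, and 100 subjects across all sites, we can detect effect sizes larger than 0.40". The section concludes that the planned sample "will provide adequate power to detect changes in craving and opioid use".
- **Introduction**: "Our central hypothesis is that DLPFC-targeted iTBS will significantly reduce both opioid craving and opioid use".
- **Study design and Discussion**: these lean towards craving. The design is described as aimed at opioid craving, and the Discussion names craving as the target, with opioid use following from it. Neither is stated as a test order.
- **Abstract, Aims**: the primary aim is whether active iTBS "results in reduced craving and opioid use, and higher treatment retention, relative to sham". Retention is also listed among the assessments in the abstract's Methods and in the captions of Figs 2 and 3. It does not appear in Sample size, in the primary or secondary outcome, or in either analysis subsection.

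**The concern.** One error rate and one power figure can describe a trial's primary conclusion only if the document says which result, or combination of results, makes that conclusion. Here two tests lead to it and no rule combines them.

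If either significant result may support the claim that iTBS works, two 5% tests give more than a 5% chance of a false claim. If both must be significant, 80% power for each does not give 80% power for the pair. A split result, significant on one outcome and not on the other, has no agreed interpretation.

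Retention raises a related problem. The abstract promises an answer on it as part of the primary aim, and the sections that should deliver that answer do not mention it.

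**Working it through.** **Inputs from the documents:** 5% type 1 error, 80% power, 100 completers and an effect size of 0.40 (Sample size); two primary tests (Primary outcome analysis).

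**Assumptions, because the documents are silent:** each test is two-sided at 5%, inferred from the only stated error rate. The correlation between the two test statistics is not given, so 0 to 0.9 is shown.

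**The plan's own figure.** With 50 completers per arm (1:1 assumed), two-sided 5%, 80% power and no gain from covariates, the detectable effect is (1.960 + 0.842) × √(2/50) = 0.56, not 0.40. The 0.40 would be reached if covariates explained about 49% of the variance, which is not stated. That is a separate question. Everything below takes the stated 80% per outcome as given.

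**Either outcome suffices.** At correlation 0 the family-wise error is 1 − 0.95² = 0.0975. For positive correlation it is 1 − P(|Z1| < 1.960 and |Z2| < 1.960) under a bivariate normal.

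**Both outcomes required.** The error stays at or below 5%, because a false joint claim needs a false positive on at least one specified test. With 80% power each, the mean of Z is 1.960 + 0.842 = 2.802. Joint power is P(Z1 > 1.960 and Z2 > 1.960), which at correlation 0 is 0.80² = 0.64.

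| Correlation | Family-wise error, either suffices | Power for at least one | Joint power, both required |
|---|---|---|---|
| 0 | 9.75% | 96% | 64% |
| 0.5 | 9.1% | 91% | 69% |
| 0.9 | 7.0% | 85% | 75% |

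For 80% joint power at correlation 0, each test needs √0.80 = 0.894 power. The sample then scales by ((1.960 + 1.250)/2.802)², about 1.31, which is about 131 completers against 100.

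**Testing at 2.5%.** The critical value becomes 2.241. Power per outcome is Φ(2.802 − 2.241) = 71%. To keep 80%, the detectable effect rises by (2.241 + 0.842)/2.802 = 1.10, from 0.40 to 0.44.

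**Craving first, opioid use only if craving succeeds.** The overall error is 5%, and the 80% power holds for craving. Power to claim both is the joint figure in the table, 64% to 75%.

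**Retention, section by section.** It is in the primary aim (abstract) and among the assessments (abstract Methods, Figs 2 and 3). It is absent from Sample size, Primary outcome, Secondary outcome and both analysis subsections.

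**The case against.** The strongest reply is that a journal article may leave a multiplicity rule, and a definition of retention, to a full protocol or SAP that is not shown. That has some weight. But this article has its own Statistical analysis plan section setting out both primary tests, and its sample size statement attaches one error rate and one power to both. What counts as primary success is a premise of that statement. A separate document also cannot remove the mismatch between the abstract's aim and the outcome sections.

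Several stronger readings are tempting, and the documents do not support them:

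- **That a stated property fails under every rule.** It does not. A craving-first rule would preserve both the 5% and the 80% for craving, and the Study design and Discussion lean that way without saying so. The power sentence can also be read as 80% per outcome, in which case joint power of 64% to 75% contradicts nothing stated.
- **That both outcomes are already required.** The Introduction states a hypothesis about both outcomes. It does not set a success criterion.
- **That joint power is only about 27% to 35%.** That range (correlation 0 to 0.5) starts from 52% power per outcome at an effect of 0.40 without covariates. It borrows the separate sample size question and ignores the planned adjustment for baseline, age and sex.
- **That the error is 14.3%.** That is 1 − 0.95³, with retention as a third primary test. The article gives retention no test.
- **That a split result is likely.** Nothing in the documents bears on its probability.

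The retention mismatch is also narrow. The body's hypothesis and primary outcome name only craving and use, so correcting the abstract's wording would resolve it.

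**Conclusion.** The point holds in this form. The article names two primary outcomes, tests each separately without a multiplicity rule, and states one 5% error and one 80% power for both. If either outcome may carry the claim, the error is 9.75% to 7.0% for correlations of 0 to 0.9. If both are required, the error is controlled and joint power is 64% to 75%. Until a rule is written down, the stated pair of figures cannot be attached to the primary conclusion.

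These sizes rest on two-sided 5% tests, on the assumed correlation range, and on accepting the stated 80% per outcome. They do not depend on whether 0.40 is the right detectable effect.

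The retention wording in the abstract's primary aim disagrees with the outcome and analysis sections and needs reconciling. A reader might also infer that opioid use must be demoted. It need not be: the Primary outcome section gives the two measures equal standing, and more than one rule would settle the matter.

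**What to change.** State one decision rule in the Primary outcome and Primary outcome analysis sections before any comparison by arm. Staff delivering TMS know the allocation and recruitment began in June 2026, so the rule should be dated and recorded soon. Any of these would do:

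- **Fixed sequence:** craving at week 10 first, then opioid use at 5% only if craving is significant. This fits the emphasis in the Study design and Discussion sections.
- **Holm:** keep both as co-primary, with the smaller p-value tested at 2.5% and the other at 5% if the first succeeds.
- **Both required:** declare that success needs significance on both outcomes.

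Then restate Sample size to match. With the fixed sequence, say that 5% and 80% apply to craving only. With a 2.5% first step, report about 71% power per outcome at that level, or a detectable effect about 10% larger. With both required, report joint power over a range of correlations.

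For retention, either remove it from the primary aim or list it as a secondary outcome, with a definition and a comparison between arms using the retention data already planned.

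The cost is a protocol amendment at both IRBs and a registry update. No extra participants are needed to control the error rate. The price is some power (per outcome under Holm, jointly if both are required), or, under the fixed sequence, no confirmatory claim on opioid use if craving fails.
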